#### Exclusion Criteria

Patients are ineligible for this study if they meet any of the following criteria: 1) diagnosis of type 1 diabetes, gestational diabetes, or other special types of diabetes; 2) diabetes-related complications as the main presentation, including serious heart, lung, liver, kidney, or brain complications, or other serious primary diseases; 3) presence of diabetic ketoacidosis, hyperosmolar non-ketotic diabetic coma, severe infection, or history of surgery in the past month; 4) history of serious gastrointestinal diseases such as peptic ulcer, gastrointestinal bleeding, gastroparesis, pyloric stenosis, or gastric shunt; 5) diagnosis of psychiatric disease including alcoholism and/or psychoactive substance abuse, drug abuse, or addiction; 6) pregnancy, lactation, or intention to become pregnant; 7) history of clinical trial participation at the present or in the past month; and 8) presence of other diseases that may affect the effectiveness of study treatments or likelihood of study completion and loss to follow-up, including the unstable living or working environment, as judged by the qualifying investigator.

### Sample Size

Based on a previous study, the HbA1c level generally reduced by 1.0 and 0.9% using metformin and JTTZF for treatment, respectively. (Zhao, 2013; China Diabetes Society, 2021). The sample size was calculated by assuming a test power of 80% and a confidence level of 95%, Z_1-alpha/2_ = 1.960, alpha = 5% for the two-tailed hypothesis, Z_1-beta_ = 0.842, sigma = 0.024. A total of 38 patients are required in each group. Allowing for a 20% dropout rate during the follow-up period, the sample size was increased to at least 48 patients for each group, thus, creating a total sample of 96 patients. PASS software (version 11.0; NCSS, LLC. Kaysville, UT, United States) was used for these calculations.

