Traditional Chinese Medicine (TCM) approaches reportedly improve glycaemic control, blood lipid levels, and weight management. (Wu et al., 2020). In fact, a TCM herbal formula may ameliorate blood glucose and lipid levels by shifting the composition of the gut microbiota. (Tong et al., 2018). The Jiangtang Tiaozhi (JTTZ) recipe has been used to treat patients with T2DM with dyslipidaemia for many years. (Zhao, 2013). Interestingly, the findings from a multi-centre trial suggested that it is safe and effective in the management of the blood glucose levels, lipid levels, and weight in patients with T2DM with obesity and hyperlipidaemia. (Yu et al., 2018). The formula consists of eight Chinese herbs, including Aloe [*Aloe vera* (L.) Burm. f. or *Aloe ferox* Mill. (Asphodelaceae)], *Coptidis rhizoma* [*Coptis chinensis* Franch., *Coptis teeta* Wall., or *Coptis deltoidea* C.Y.Cheng and P.K.Hsiao (Ranunculaceae)], *Anemarrhenae rhizoma* [*Anemarrhena asphodeloides* Bunge (Asparagaceae)], red yeast rice [*Fermentum Rubrum* (Aspergillaceae)], bitter melon [*Momordica charantia* L. (Cucurbitaceae)], *Salvia miltiorrhizae radix et rhizoma* [*Salvia miltiorrhiza* Bunge (Lamiaceae) ], *Schisandrae chinensis fructus* [*Schisandra chinensis* (Turcz.) Baill. (Schisandraceae)], and *Zingiberis rhizoma* [*Zingiber officinale* Roscoe (Zingiberaceae)]. In the TCM theory, the JTTZ recipe clears the excess heat in the stomach and intestines, thus alleviating patients’ symptoms. However, the mechanism underlying the clinical efficacy of the JTTZ recipe remains unknown. We hypothesised that the JTTZ may exert a therapeutic effect equal to or better than that exerted by metformin among patients with T2DM with dyslipidaemia, and that this effect may be mediated by the modulation of metabolites secreted by the gut microbiota. Therefore, a randomised, positive drug parallel-controlled, open-label clinical trial was designed; 16S rRNA gene sequencing as well as gas chromatography/time-of-flight mass spectrometry analyses will be performed to explore these mechanisms.

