## Methods

### Study Design

This study is a randomised, positive drug parallel-controlled, open-label, non-inferiority clinical trial in patients with glucose and lipid metabolism disturbances. In total, 96 patients diagnosed with T2DM and dyslipidaemia will be recruited for this study. The patients will be randomly divided into two groups and treated with the JTTZ recipe or metformin for 12 weeks. This study protocol follows the Standard Protocol Items: Recommendations for Interventional Trials. (Chan et al., 2013). (Supplementary File S1). The study flow is illustrated in Figure 1. All information related to the treatment schedule is presented in Table 1.

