### Randomisation and Allocation

The randomisation scheme was generated by the Administration Office of Drug Clinical Trial in the Guang’anmen Hospital, using the PROC PLAN procedure in SAS statistical software (version 9.4; SAS Institute, Cary, NC, United States), with a 1:1 allocation ratio to the experimental and control groups (total sample, 96 patients). The randomisation code will be released by the interactive web response system to conceal group allocation. Eligible patients will be assigned to the interventions by research assistants, according to the unique number from the randomisation scheme, the patients will receive study treatment assigned by the scheme.

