### Primary Outcomes

The changes of HbA1c levels are the primary study outcomes Besides, the rates of effectively regulated HbA1c, FPG, 2 h-PG, TG, and LDL-C levels will be calculated based on the number of patients who make the target achievement. The HbA1c level ≤7%, FPG level ≤7.0 mmol/L (126 mg/dl), 2 hP G level ≤10.0 mmol/L (180 mg/dl), TG level ≤1.7 mmol/L (150 mg/dl), LDL-C level ≤3.3 mmol/L (130 mg/dl) will be set as the target achievement. The FPG levels will be tested during the screening period, before intervention, and every 4 weeks during the treatment period. The levels of HbA1c, 2 h-PG, TG, and LDL-C will be recorded during the screening period, at the beginning and at the end of the12-week treatment period.

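### The stated inputs give 38 per group only if sigma = 0.024 is used as a variance, and as printed the 80% power is for detecting a 0.1-point difference, not for non-inferiority

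*Protocol article*

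**What the plan says.** Study Design calls the trial a "randomised, positive drug parallel-controlled, open-label, non-inferiority clinical trial". The Background hypothesis is that "JTTZ may exert a therapeutic effect equal to or better than that exerted by metformin". Primary Outcomes states that "The changes of HbA1c levels are the primary study outcomes", and this is the endpoint on which the trial is sized.

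Sample Size takes its effect from earlier work: "the HbA1c level generally reduced by 1.0 and 0.9% using metformin and JTTZF for treatment, respectively". It sets "alpha = 5% for the two-tailed hypothesis", "assuming a test power of 80% and a confidence level of 95" per cent, and normal quantiles of 1.960 and 0.842. The result is "sigma = 0.024. A total of 38 patients are required in each group". A 20% dropout allowance then raises this to 48 per group, 96 in total. Randomisation and Allocation confirms equal groups: "with a 1:1 allocation ratio to the experimental and control groups (total sample, 96 patients".

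No non-inferiority margin appears among these inputs or elsewhere in the article. Statistical Analysis sets significance by two-sided p-values.

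**The concern.** Two things do not fit. First, sigma is the usual symbol for an SD. An SD of 0.024 against a difference of 0.1 would need almost no patients, so 38 cannot follow from the inputs as labelled.

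Second, the only effect in the calculation is an expected shortfall of JTTZ against metformin, tested with a two-tailed hypothesis. A non-inferiority calculation needs a margin, and its power comes from the distance between that margin and the assumed true difference. Without a margin, a reader cannot tell that 80% is the chance of success for the declared objective.

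This paragraph is the article's only justification for 96 patients. If its power figure belongs to another question, or rests on an implausibly small SD, an inconclusive or non-significant result will be hard to interpret.

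**Working it through.** **Inputs, all from Sample Size:** difference 1.0 − 0.9 = 0.1 HbA1c points; z = 1.960 and 0.842, sum 2.802, squared 7.851; sigma = 0.024 with no unit; dropout 20%. Allocation is 1:1.

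**Formula for two means, per group:** n = 2 × (1.960 + 0.842)² × variance / 0.1².

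**Step 1. Reproduce the plan's figure.**

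| Reading of 0.024 | Calculation | n per group |
|---|---|---|
| SD, as labelled | 2 × 7.851 × 0.024² / 0.01 = 0.90 | 1 (3 by t-test) |
| Variance (SD = √0.024 = 0.155) | 2 × 7.851 × 0.024 / 0.01 = 37.69 | 38 (39 by t-test) |

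Other readings also fail. One-sided 5% with 0.024 as a variance gives 30. Treating both figures as proportions (difference 0.001, SD 0.024) gives 9,042. The dropout step is correct: 38 / 0.8 = 47.5, so 48.

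**Step 2. What the 80% refers to.** With SD 0.155 and 38 per group, power to detect a 0.1 difference is 80.3% by the normal approximation and 79% by the t-test. This is power to show that the two treatments differ.

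**Step 3. Could the same figure be a non-inferiority calculation?** With one-sided alpha 0.025 the critical value is also 1.960, and the formula becomes n = 2 × 2.802² × variance / (margin − true difference)². It gives 38 at variance 0.024 whenever margin minus true difference is 0.1:

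- Margin 0.2 with the stated 0.1 deficit gives 38.
- Margin 0.1 with no true difference gives 38, but this contradicts the stated reductions.
- Margin 0.1 with the stated 0.1 deficit puts the truth on the margin, and power is 2.5%.

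The article states none of these margins.

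**Step 4. The implied SD.** With SD 0.155, about 95% of patients would have a change within 1.96 × 0.155 = 0.30 points of a mean reduction of 0.9 to 1.0.

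**Step 5. Illustration.** The SDs of change and the margin of 0.4 are assumptions, not in the document. There are 38 per group, and power is t-based. The non-inferiority column uses the stated 0.1 deficit, so the distance to the margin is 0.3.

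| Assumed SD | Power to detect 0.1 (two-sided) | Non-inferiority power, margin 0.4 | 95% CI half-width |
|---|---|---|---|
| 0.8 | 8% | 36% | 0.37 |
| 1.0 | 7% | 25% | 0.46 |
| 1.2 | 6% | 19% | 0.55 |

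**The case against.** The strongest reply is that the printed formula is algebraically a non-inferiority formula when margin minus true difference equals 0.1, and that two-sided 5% uses the same critical value as one-sided 0.025. The article refers to a full trial protocol that is not shown, and a margin could be stated there. This stands in part. It would be too strong to say that the calculation cannot have been intended for non-inferiority. What remains is that the paragraph, as printed, gives 0.1 as the expected difference, names no margin and does not show such a calculation. A margin stated elsewhere would also leave the mismatch between sigma = 0.024 and 38 unexplained.

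It is also fair that nothing in the document says 0.024 was entered as a variance. That is an inference from the match with 37.69. Whichever reading is taken, either the label or the result is wrong.

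A reader might go further in two ways that the documents do not support:

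- **That the trial has about an 80% chance of declaring JTTZ worse.** That holds only for 38 completers per group, SD 0.155 and a true 0.1 deficit. It is not a statement about the intention-to-treat analysis.
- **That analysing dropouts by their last record would alone raise the SD to about 0.4.** That needs all 20% to leave before week 12 with zero change. Sample Size places the dropouts in the follow-up period, and Table 1 runs to week 48. Patients lost after week 12 would already have a 12-week HbA1c.

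**Conclusion.** The point holds in a bounded form. As labelled, the inputs give 1 patient per group, not 38. The 38 is reproduced only with 0.024 as a variance, and the calculation as printed is a two-tailed one for a 0.1-point difference favouring metformin. The 80% is therefore not shown to apply to the declared non-inferiority design. These conclusions use only figures printed in the article.

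The size of any power shortfall cannot be fixed from the article, because it gives neither a margin nor a usable SD. The 19% to 36% in the illustration depends on the assumed SDs of 0.8 to 1.2 and the assumed margin of 0.4. It shows how sensitive the power is, and it is not an estimate for this trial. The paragraph should be corrected, since it is wrong as written and cheap to put right.

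**What to change.** Keep 96 patients and rewrite the Sample Size paragraph as a non-inferiority calculation on the change in HbA1c. State:

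- the margin, with its justification;
- one-sided alpha 0.025, which keeps the present critical value of 1.960;
- the assumed true difference, 0.1 points in favour of metformin;
- an SD of change taken from the cited previous study, labelled as an SD and given with its unit.

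Remove sigma = 0.024. Replace the 80% claim with the power and the expected 95% CI half-width that 38 evaluable (48 randomised) per group give, over a range of SDs around the sourced value.

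The cost is one paragraph and no extra patients. The downside is that the stated power will probably be less favourable.

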### Randomisation and Allocation

The randomisation scheme was generated by the Administration Office of Drug Clinical Trial in the Guang’anmen Hospital, using the PROC PLAN procedure in SAS statistical software (version 9.4; SAS Institute, Cary, NC, United States), with a 1:1 allocation ratio to the experimental and control groups (total sample, 96 patients). The randomisation code will be released by the interactive web response system to conceal group allocation. Eligible patients will be assigned to the interventions by research assistants, according to the unique number from the randomisation scheme, the patients will receive study treatment assigned by the scheme.

### Test Drugs and Blinding

The JTTZ recipe granules used in the trial are provided by the Tianjiang Pharmaceutical Co., Ltd. (Jiangyin, Jiangsu Province, China) The metformin tablets are provided by the Guang’anmen Hospital and produced by the Shanghai Shiguibao Pharmaceutical Co., Ltd. (Shanghai, China). All drugs meet the requirements of good manufacturing practice. Although the study is open-label, the research assistants who assign patients to groups will not be aware of treatment allocation before group assignment is provided. Efficacy assessment and analysis of the results will be performed by assessors and statisticians blinded to the group allocation. All samples and data will be anonymised before analysis and evaluation.

### Interventions

Patients in the JTTZ recipe group will receive the JTTZ recipe granules (30 g per bag), one bag at a time, twice a day, to be taken with warm water after meals. Patients in the metformin group will receive 500 mg metformin tablets at a time, three times a day, to be taken with meals. The allocated interventions may be modified. In addition, this study applies the add-on therapy and the former administration of lipid-lowering agents will not be withdrawn. If AEs or voluntary withdrawal occurs, the interventions will be discontinued. Laboratory tests and drug packing return will be arranged to monitor and improve adherence.

### Outcome Measures

Demographic and clinical characteristics of the patients, including age, sex, height and weight, medical and treatment history, and examination findings, among others, will be recorded in the CRFs during a 1-week screening period and every 4 weeks during the treatment period.

### Primary Outcomes

The changes of HbA1c levels are the primary study outcomes Besides, the rates of effectively regulated HbA1c, FPG, 2 h-PG, TG, and LDL-C levels will be calculated based on the number of patients who make the target achievement. The HbA1c level ≤7%, FPG level ≤7.0 mmol/L (126 mg/dl), 2 hP G level ≤10.0 mmol/L (180 mg/dl), TG level ≤1.7 mmol/L (150 mg/dl), LDL-C level ≤3.3 mmol/L (130 mg/dl) will be set as the target achievement. The FPG levels will be tested during the screening period, before intervention, and every 4 weeks during the treatment period. The levels of HbA1c, 2 h-PG, TG, and LDL-C will be recorded during the screening period, at the beginning and at the end of the12-week treatment period.

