### Eligibility Criteria

#### Diagnostic Criteria of T2DM

The diagnostic criteria for T2DM are based on the *Guideline for the prevention and treatment of type 2 diabetes mellitus in China* (2020 edition), (China Diabetes Society, 2021), and include diabetic symptoms (increased thirst and urine volume, unexplained weight loss) plus any of the following: 1) random blood plasma glucose (blood glucose at any time of the day regardless of the time of last meal) levels ≥11.1 mmol/L (200 mg/dl); 2) fasting plasma glucose (FPG) level ≥7.0 mmol/L (126 mg/dl); 3) 2-h plasma glucose (2-h PG) level ≥11.1 mmol/L (200 mg/dl); and 4) glycated haemoglobin (HbA1c) level ≥6.5%.

In the absence of any symptom of diabetes, blood glucose measurements will be repeated on another day to confirm the diagnosis.

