#### Inclusion Criteria

Patients are eligible for this study if they meet the following criteria: 1) age of 18–70 years at the time of enrolment; 2) diagnosis of T2DM plus 7.0 mmol/L (126 mg/dl) ≤ FPG level ≤13.9 mmol/L (250 mg/dl), or 2-h PG level ≥11.1 mmol/L (200 mg/dl) at the time of enrolment; 3) diagnosed with dyslipidaemia plus LDL-C level ≥3.4 mmol/L (130 mg/dl) and having TG level >1.7 mmol/L (150 mg/dl) at the time of enrolment; 4) have a body mass index ≥24.0 kg/m^2^ or waist circumference ≥90 cm for men and ≥80 cm for women; 5) failure to take anti-diabetic drugs regularly to reach normal blood glucose and lipid levels after diet control and exercise therapy before enrolment; 6) TCM syndrome differentiation as excess heat in the stomach and intestines syndrome; and 7) provision of signed informed consent form.

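### The HbA1c, FPG and 2-h PG target rates take no account of patients who may already be at target on entry

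*Protocol article*

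**What the plan says.** All references are to the protocol article.

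- **Primary Outcomes** names HbA1c change and then adds target rates for HbA1c, FPG, 2-h PG, TG and LDL-C, which "will be calculated based on the number of patients who make the target achievement". The glycaemic limits are "The HbA1c level ≤7%, FPG level ≤7.0 mmol/L (126 mg/dl), 2 hP G level ≤10.0 mmol/L (180 mg/dl". The lipid limits are "TG level ≤1.7 mmol/L (150 mg/dl), LDL-C level ≤3.3 mmol/L (130 mg/dl) will be set as the target achievement".
- **Inclusion Criteria**, item 2, asks for a T2DM diagnosis plus "7.0 mmol/L (126 mg/dl) ≤ FPG level ≤13.9 mmol/L (250 mg/dl), or 2-h PG level ≥11.1 mmol/L (200 mg/dl) at the time of enrolment". One of the two glucose limbs is enough, and no HbA1c limit is set. Item 3 requires LDL-C of at least 3.4 mmol/L and TG above 1.7 mmol/L.
- **Diagnostic Criteria of T2DM** lists "glycated haemoglobin (HbA1c) level ≥6.5"% as one of four alternative laboratory criteria.
- **Statistical Analysis** tests count data by chi-square or Fisher's exact test and mentions no baseline covariate.
- **Removal, Dropout, and Termination Criteria** has dropouts analysed on their last recorded value.
- **Table 1** measures HbA1c and 2-h PG in the treatment phase only at weeks 0 and 12. FPG is also measured at weeks 4 and 8.
- **Study Design** calls the trial non-inferiority.

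**The concern.** A rate meant to show that treatment brought a marker under control should not credit treatment for patients who needed no change. The entry rules and the glycaemic targets do not mesh, so some patients may meet a target before the first dose. If they remain there, they count as successes in whichever arm they join. That raises both rates and leaves less room for the arms to differ. In a trial labelled non-inferiority, a smaller difference leans towards the conclusion that the trial seeks. The planned unadjusted test does nothing to separate baseline status from response.

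**Working it through.** **1. The plan's own figure.** The Sample Size section rests on HbA1c change, not on the rates. With a difference of 0.1 (1.0 versus 0.9) and 0.024 read as a variance, n = 2 × 0.024 × (1.960 + 0.842)² / 0.1² = 37.7, so 38 per group. Then 38 / (1 − 0.20) = 47.5, so 48. The stated figures are reproduced, and this point does not alter them. No size or response rate is given for the target rates.

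**2. Can a patient enter at target?**

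| Marker | Target | Entry condition | At target on entry? |
|---|---|---|---|
| HbA1c | ≤7% | none; 6.5% can support the diagnosis | yes, e.g. 6.6% |
| FPG | ≤7.0 mmol/L | 7.0–13.9, or waived if 2-h PG ≥11.1 | yes, through the 2-h PG limb, or at exactly 7.0 |
| 2-h PG | ≤10.0 mmol/L | ≥11.1, or waived if FPG is 7.0–13.9 | yes, through the FPG limb |
| TG | ≤1.7 mmol/L | >1.7 | no |
| LDL-C | ≤3.3 mmol/L | ≥3.4 | no |

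Inclusion item 5 (glucose and lipids not yet normal) gives no cut-off per marker, so it does not close the gap.

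**3. Effect on the rates.** Let q be the share at target on entry, s the share of those still at target at week 12, and p the week-12 rate among those who entered above target. Subscripts 1 and 2 denote the arms.

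Rate = q·s + (1 − q)·p

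Difference = q(s₁ − s₂) + (1 − q)(p₁ − p₂)

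If s₁ = s₂, the difference is (1 − q)(p₁ − p₂). The documents give none of q, s or p. Assuming s = 1 and p = 0.50 versus 0.30:

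- q = 10%: 0.10 + 0.90 × 0.50 = 0.55 versus 0.10 + 0.90 × 0.30 = 0.37; difference 0.18
- q = 20%: 0.60 versus 0.44; difference 0.16
- q = 30%: 0.65 versus 0.51; difference 0.14

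**4. When the direction fails.** With q = 30%, p = 0.50 versus 0.40 and unequal retention s = 0.95 versus 0.70, the difference is 0.30 × 0.25 + 0.70 × 0.10 = 0.145. That is larger than the 0.10 among patients above target.

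**5. Power, as an illustration.** Take 48 per arm, a two-sided 5% test, assumed p = 0.60 versus 0.40 and s = 1. The all-patients comparison has power 36% at q = 20% and 30% at q = 30%. Restricted to the 48(1 − q) patients per arm above target, power is 42% and 37%. Under these assumptions the smaller denominator does not cost power.

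**6. Last-record rule.** A patient who leaves before week 12 has week 0 as the last HbA1c and 2-h PG value. If that value was at target, the patient counts as a success without any on-treatment measurement. Suppose the planned 20% dropout all fell before week 12, was unrelated to entry status, and q were 20%. The expected number is then 48 × 0.20 × 0.20 = 1.9 patients per arm.

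**The case against.** **The all-patients rate is a legitimate estimand.** The proportion of all randomised patients at target at week 12 is a valid quantity, and randomisation balances q between arms in expectation. The comparison is unbiased for that quantity. This stands. The rates are inflated only if they are read as the effect of treatment on patients who needed it, which is how a rate of effective regulation will be read.

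**The denominator is not stated.** The article gives none, and a fuller protocol may. That is fair as to the denominator. But the targets, the entry limits and the unadjusted test are all fixed in this document, and their mismatch is visible here.

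**The affected share may be small.** No patient can be inside both the FPG and 2-h PG targets on entry, except with FPG at exactly 7.0. Only HbA1c is wholly unrestricted. This stands and limits the size.

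**The rates may not be the main endpoint.** Primary Outcomes puts HbA1c change first, and the trial is sized on it. The Abstract, however, names the rates as the primary outcome, so they cannot be set aside.

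**Stronger readings that a reader might infer.**

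- That patients at target on entry are automatic successes and the difference must shrink. Step 4 shows that it can grow, and nothing in the documents fixes retention.
- That LDL-C has the same flaw, because "LDL-C level ≤3.3 mmol/L (130 mg/dl) will be set as the target achievement" and "LDL-C level ≥3.4 mmol/L (130 mg/dl" share one mg/dl figure. In mmol/L, the lead unit, the limits do not overlap, and the bracket is a matter of rounding.
- That a false non-inferiority conclusion would follow. The article ties no margin to the rates, so this cannot be shown.
- That the denominator must be restricted to patients above target. That is debatable. It gives each marker its own population, and selecting on a single high week-0 value invites regression to the mean.

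**Conclusion.** The point holds for the three glycaemic rates. The entry rules allow patients already at target, the rate definition has no condition on the starting value, and the planned test does not adjust for it, so these rates mix baseline status with response. The arm difference shrinks by the factor (1 − q) provided that patients at target on entry stay there about equally in both arms. For an assumed q of 10–30%, a 20-point difference becomes 18 to 14 points. The true size is unknown, and the direction is conditional on similar retention. The last-record rule adds a smaller problem for HbA1c and 2-h PG. The TG and LDL-C rates, the HbA1c change outcome and the sample size are untouched. The matter is worth correcting, but it does not invalidate the trial.

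**What to change.** 1. Compare the HbA1c, FPG and 2-h PG rates between arms with a logistic model containing treatment and the week-0 value of that marker, in place of the unadjusted test.
2. Report the number at target at week 0 for each of the three markers by arm.
3. Give, as a supporting analysis, the rate among patients above the relevant target at week 0.
4. In the same tables, show how many successes for HbA1c and 2-h PG rest on a carried-forward week-0 value.

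Table 1 already schedules all three markers at week 0, so no new measurement is needed. The cost is a little more analysis work and smaller denominators in the supporting analysis. The adjusted odds ratio is not a difference in proportions, so the crude rates should still be shown beside it.
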